### Participant timeline {13}

Patients will be followed up until the 28th day post-enrolment or hospital discharge, whichever occurs first. Data collected will be restricted to the parameters that are necessary to define clinical characteristics and will be obtained from routine laboratory investigations and hospital records (Fig. 2). This includes baseline demographics, outcome measures, physiological parameters, operative data, therapeutic interventions, death and other adverse events.

**Fig. 2 Fig2:**
[figure not shown]
Data collection timeline (SPIRIT figure). CRRT, continuous renal replacement therapy; eGFR, estimated glomerular filtration rate; Hb, haemoglobin; Hct, haematocrit; ICU, intensive care unit; LVEF, left ventricular ejection fraction; SCr, serum creatinine

### Sample size {14}

The sample size for the study was determined by a priori power analysis. The anticipated incidence of AKI in the comparator group was based upon a cohort of over 25,000 patients that reported AKI in 30% of patients undergoing cardiac surgery [1]. Based on this estimate, the inclusion of 590 patients will achieve 80% power to detect a 10% absolute risk reduction in the risk of AKI (2-sided *p* = 0.05).

### Recruitment {15}

Recruitment will take place at metropolitan teaching hospitals that see a large number of cardiac cases. This will allow sufficient enrolment to reach the target sample size in a timely manner.

## Assignment of interventions

### Sequence generation {16a}

A permuted block, computer-generated, randomisation sequence with fixed block size, stratified by hospital and eGFR (< 60 mL/min/1.73 m^2^ or > 60 mL/min/1.73 m^2^) will be used to allocate participants in a 1:1 ratio.

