## Trial design {8}

The ALBICS (ALBumin Infusion and acute kidney injury following Cardiac Surgery) study is a multicentre, parallel-group, open-label, prospective, randomised controlled, superiority trial.

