### Concealment mechanism {16b}

Patients will be allocated using REDCap (Research Electronic Data Capture), a computer-based software for data collection. REDCap will use the prepared randomisation schedule to determine the allocation of the participant in a traceable manner, such that the treatment group is not knowable prior to allocation and cannot be changed after it. While blinding clinicians to treatment allocation is desirable, it is not deemed feasible for this study. We minimise bias through allocation concealment and evaluation of objective laboratory-based data.

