### Implementation {16c}

The allocation sequence will be generated by a person not involved with enrolment or future analysis. Participants will be screened and randomised on admission to intensive care by a site investigator or member of research support staff.

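### One fixed block size within hospital-by-eGFR strata, in an open-label trial randomised by site staff, lets some allocations be deduced if the size is known or inferred

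*Protocol article*

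**What the plan says.** Sequence generation {16a} sets out "A permuted block, computer-generated, randomisation sequence with fixed block size, stratified by hospital and eGFR", split at 60 mL/min/1.73 m², which "will be used to allocate participants in a 1:1 ratio". The block size is not given.

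Trial design {8} describes a "multicentre, parallel-group, open-label, prospective, randomised controlled, superiority trial". Concealment mechanism {16b} adds: "While blinding clinicians to treatment allocation is desirable, it is not deemed feasible for this study".

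The same section says that REDCap applies the prepared schedule "such that the treatment group is not knowable prior to allocation and cannot be changed after it", and then: "We minimise bias through allocation concealment and evaluation of objective laboratory-based data".

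On who does what, Implementation {16c} states "The allocation sequence will be generated by a person not involved with enrolment or future analysis", and "Participants will be screened and randomised on admission to intensive care by a site investigator or member of research support staff".

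Study setting {9} lists six hospitals, so there are 6 × 2 = 12 separate allocation sequences.

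**The concern.** Concealing the list is not the same as making the next allocation unpredictable. In a 1:1 permuted block, once one arm has used its half of the block, every remaining place goes to the other arm. Four stated features together let an observer see this happen:

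- past treatment is visible, because the active arm is a bedside infusion lasting 15 h;
- blocks run within hospital, so one team sees the whole history of its strata;
- the block length does not change, so the arm counts return to equality at every multiple of it, which allows it to be inferred;
- the people who see that history also decide whom to screen and randomise.

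What is at stake is selective enrolment: a patient judged to be at high or low risk of AKI is included or passed over according to the arm that comes next. An objective laboratory outcome guards against biased ascertainment, but not against a difference between the patients who enter each arm. Blinding {17a} defends the open-label design on the ground that the outcomes are remote from the intervention. That too concerns outcomes and not entry. The main comparison is a chi-squared test, which would carry any such imbalance into the result.

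**Working it through.** **Base figure.** The article gives no figure for predictability. Its total of 590 is used here only to turn shares into counts, and it reproduces. With 30% versus 20%, two-sided 0.05 and 80% power:

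n per arm = [1.960·√(2 × 0.25 × 0.75) + 0.8416·√(0.21 + 0.16)]² / 0.10² = (1.200 + 0.512)² / 0.01 ≈ 293.1, rounded up to 294, or 588 in total. With 295 per arm the power is 80.2%.

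**Inputs.** The 1:1 ratio, fixed size and strata come from {16a}; open treatment from {8} and {16b}; six hospitals from {9}. The block size B is an assumption, so a range is shown.

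**Certain allocations.** The expected share of places forced by earlier ones in a completed block is 1/(B/2 + 1). For B = 4 this can be checked by hand. Of the six arrangements, AABB and BBAA each have two forced places and the other four have one each. That makes 8 of 24 = 1/3.

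**Guessing.** The second share is the rate of correct guesses when always naming the arm that is behind and tossing a coin at ties. For B = 4, AABB and BBAA score 2.5 each and the other four score 3 each: 17/24 = 70.8%.

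| Assumed B | Certain share | Of 590 | Correct guesses |
|---|---|---|---|
| 2 | 50% | 295 | 75.0% |
| 4 | 33.3% | 197 | 70.8% |
| 6 | 25% | 148 | 68.3% |
| 8 | 20% | 118 | 66.6% |
| 10 | 16.7% | 98 | 65.3% |
| 12 | 14.3% | 84 | 64.3% |

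Simple randomisation gives 50% correct guesses. The certain shares are upper bounds: they suppose that the size is known from the start and that a correct tally is kept for each stratum. Incomplete last blocks lower them slightly. In a stratum of 49 (590/12), B = 4 gives 32.7% and B = 6 gives 24.4%.

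**Effect of varying the size.** Strata of 49 patients were simulated 3,000 times. The observer knows the set of sizes but not the size of the current block.

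| Scheme | Certain share | Best-guess rate |
|---|---|---|
| Fixed 4 | 32.7% | 70.4% |
| Fixed 6 | 24.4% | 68.0% |
| Random 4/6 | 5.6% | 68.8% |
| Random 2/4/6 | 3.9% | 69.8% |
| Random 4/6/8 | 2.4% | 67.5% |

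Varying the size removes most of the certainty and leaves guessing almost unchanged.

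**Illustration of consequence (assumed, and deliberately extreme).** Suppose that every forced place at B = 4 were exploited, with patients at 25% risk steered to one arm and 35% to the other. The bias would be 0.333 × 10 = 3.3 percentage points, a third of the 10-point target effect. The standard error is √(2 × 0.3 × 0.7/295) ≈ 3.8 points, so the test statistic shifts by about 0.88 and the two-sided type I error rises from 5% to about 14%. At B = 8 the bias would be 0.20 × 10 = 2 points. The bias shrinks in proportion if only some forced places are used.

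**The case against.** The strongest reply is that prediction takes effort and the opening for misuse is narrow. With about 565 patients left (590 less the 25 reported at October 2020), spread over 12 sequences from July 2021 to the end of 2023, accrual averages about 1.6 patients per stratum per month. The two eGFR sequences at a site are interleaved. Working out the size would take deliberate tallying over months. The article does not publish the size and does not say that sites are told it; that may be settled in the full protocol, which is not shown. Eligibility rests on eGFR and procedure type, consent comes before enrolment, and randomisation is tied to ICU admission, so a patient cannot easily be moved to a later place in the block.

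Much of this stands. It makes the shares upper bounds, and it makes passing over an eligible patient a more plausible route than postponing one. It does not remove the weakness: a constant size is the feature that makes tallying informative, and neither the hidden list nor the independent generator stops deduction from visible allocations.

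A further fair objection is that varying sizes does little against guessing. That is correct. If the current size is 8, the guess rate could even rise slightly, from 66.6% to about 67.5%.

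A reader might infer that the randomisation rule flatly contradicts the statement "such that the treatment group is not knowable prior to allocation and cannot be changed after it", or defeats concealment. The documents do not support that. The sentence describes how REDCap handles the schedule, and a hidden list that cannot be altered is still concealment. It is weakened, not abolished. Nor is concealment ranked as the main safeguard; it is one of two named together.

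**Conclusion.** The point holds as a design weakness that should be fixed. The article itself fixes a single block size, within hospital, in an open trial randomised by site staff. If that size is known or inferred, at most about one third (size 4) to one seventh (size 12) of allocations can be deduced with certainty, and half only if the size is 2, which nothing in the article suggests. These figures rest on an assumed size, a correct tally by stratum and completed blocks.

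Two stronger inferences are not supported. First, there is no evidence that selection has taken place or that the primary comparison is biased; the 3.3-point figure is hypothetical. Second, it goes too far to say that no later analysis could help. Adjustment can address measured risk factors, and baseline balance can be examined by position in the block. Neither deals with unmeasured judgement at the bedside, which is why prevention is preferable.

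**What to change.** Generate the rest of the REDCap schedule with block sizes chosen at random (for example 4, 6 and 8) within the same hospital-by-eGFR strata, and withhold the sizes from sites. Amend Sequence generation {16a} to say that block sizes vary at random, without listing them. The claim in Concealment mechanism {16b} will then be better supported. For patients already randomised, report the block size in the final publication and check baseline balance by position in block.

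The gain is a fall in certain predictions to about 2–6%, depending on the mix. The best-guess rate stays at about 68–70%, and the amended text should not claim more. The sample size is unaffected.

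The cost is a protocol amendment, which may need ethics review, and a new schedule upload. Up to 12 blocks may be left part-filled at the switch. Possible imbalance within a stratum is slightly larger: with sizes up to 8 the arms can differ by 4 within a block, against 2 under fixed blocks of 4. The benefit covers only patients not yet randomised. The article reports 25 of 590 enrolled as at October 2020, which would leave about 565 to protect, fewer the later the change is made.

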### Concealment mechanism {16b}

Patients will be allocated using REDCap (Research Electronic Data Capture), a computer-based software for data collection. REDCap will use the prepared randomisation schedule to determine the allocation of the participant in a traceable manner, such that the treatment group is not knowable prior to allocation and cannot be changed after it. While blinding clinicians to treatment allocation is desirable, it is not deemed feasible for this study. We minimise bias through allocation concealment and evaluation of objective laboratory-based data.

### Implementation {16c}

The allocation sequence will be generated by a person not involved with enrolment or future analysis. Participants will be screened and randomised on admission to intensive care by a site investigator or member of research support staff.

### Blinding {17a}

While blinding is a desirable feature of clinical trials, the study outcomes are distant from the intervention and the open-label design is unlikely to influence the outcome at 28 days.

### Procedure for unblinding {17b}

Not applicable.

## Data collection and management

### Plans for assessment and collection of outcomes {18a}

All study data will be collected by research staff at each site using an electronic case report form and stored in a password-protected, traceable, database managed by Monash University. All parameters are defined in a data dictionary detailing the way in which data should be collected. The central coordinating investigators will ensure site visits for data monitoring, timely resolution of queries and correction of errata during quality control checks.

### Plans to promote participant retention and complete follow-up {18b}

The intervention is to be administered soon after ICU admission and will last a short duration of time, likely while participants are unconscious. Patients will be approached once conscious and practical to do so, to inform them of study progress and follow-up required. Obtaining data from medical records and laboratory data will ensure complete follow-up.

### Data management {19}

Study data was collected and managed using REDCap electronic data capture tool hosted and managed by Helix (Monash University) [39, 40]. REDCap is a secure, web-based software platform designed to support data capture for research studies, providing [1] an intuitive interface for validated data capture [2]; audit trails for tracking data manipulation and export procedures [3]; automated export procedures for seamless data downloads to common statistical packages; and [4] procedures for data integration and interoperability with external sources.

### Confidentiality {27}

Wherever possible, identifying information will be removed. Only de-identified data will be entered into the case report form. Identifying documents such as consent forms will be kept in locked rooms that may only be accessed by authorised personnel.

### Plans for collection, laboratory evaluation and storage of biological specimens for genetic or molecular analysis in this trial/future use {33}

Not applicable. This study evaluates data collected via routine laboratory investigation.

## Statistical methods

### Statistical methods for primary and secondary outcomes {20a}

Normality of continuous variables will be assessed and log-transformed where appropriate. Equality of variance for normally distributed variables will be assessed using Levene’s test. Between-group comparisons will be performed using chi-squared tests for equal proportion, Student’s *t* test for continuous variables with equal variance, Welch’s *t* test for continuous variables with unequal variance, and Mann-Whitney *U* test otherwise. Categorical variables will be described as frequency with proportions (%). Continuous variables will be expressed as mean ± standard deviation if normally distributed, and median with interquartile range if not normally distributed. Analysis will be performed using R version 4.0.2 (R Foundation for Statistical Computing, Vienna, Austria).

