### Outcomes {12}

The primary outcome is the proportion of patients that develop AKI within hospital stay up to Day 28 post-enrolment. AKI is defined by creatinine-based KDIGO criteria (Table 1 Pathophysiology of CSA-AKI) [38]. Patients after cardiac surgery often have polyuria in the first few hours after surgery and they are frequently given diuretic therapy after day 1 postoperatively. For this reason, urine output may not a be a reliable measure of AKI.

**Table 1 Tab1:** KDIGO creatinine-based criteria for diagnosis and staging of AKI

Stage	Serum creatinine
I	1.5–1.9 times baseline within 7 days; or ≥ 26.5 μmol/l (≥ 0.3 mg/dl) increase within 48 h
II	2.0–2.9 times baseline within 7 days
III	≥ 3.0 times baseline within 7 days; or Increase to ≥ 353.6 μmol/l (≥ 40 mg/dl); or Initiation of renal replacement therapy

Secondary and tertiary outcomes are described in Table 2. These outcomes were chosen as appropriate measures of acute deterioration or recovery, and the haemodynamic effects of albumin.

**Table 2 Tab2:** Study outcomes

Primary outcome	In-hospital AKI Stage I, II or III (proportion of patients)
Secondary outcomes	In-hospital AKI stage II and III (proportion of patients) In-hospital mortality ICU LOS (hours) Hospital LOS (days) Ventilation time (hours)
Tertiary outcomes	Peak SCr (μmol/l) Serum albumin at 24 h (g/l) Serum Hb at ICU discharge (g/l) Proportion of patients needing inotrope and/or vasopressor therapy Net fluid balance at 48 h (ml) Quantity of RBCs transfused over first 48 h (ml) Initiation of CRRT

*AKI*, acute kidney injury; *CRRT*, continuous renal replacement therapy; *Hb*, haemoglobin; *ICU*, intensive care unit; *LOS*, length of stay; *RBC*, red blood cell; *SCr*, serum creatinine

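### For the continuous secondary and tertiary outcomes, the trial data choose the scale, the test and the summary, so what is compared is not fixed in advance (minor)

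*Protocol article*

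**What the plan says.** The rule is in the Protocol article, Statistical methods for primary and secondary outcomes {20a}. It opens with "Normality of continuous variables will be assessed and log-transformed where appropriate" and continues with "Equality of variance for normally distributed variables will be assessed using Levene’s test". Student's t test is used if variances are equal, Welch's t test if they are not, and Mann-Whitney U otherwise. Variables judged normal are summarised by mean and standard deviation, the others by median and interquartile range. The section does not say how normality is judged or at what threshold. It assigns no test, scale or effect measure to any named continuous outcome.

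Table 2 under Outcomes {12} shows what the rule governs:
- **Secondary, 3 of 5:** ICU length of stay, hospital length of stay, ventilation time.
- **Tertiary, 5 of 7:** peak creatinine, 24 h albumin, haemoglobin at ICU discharge, net fluid balance at 48 h, and the entry "Quantity of RBCs transfused over first 48 h (ml").

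The primary outcome, AKI stage II/III and mortality are proportions and go to a chi-squared test.

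**The concern.** The branches answer different questions. A t test on the raw scale compares arithmetic means, a t test on logs compares geometric means, and Mann-Whitney compares ranks. These can differ in size and even in direction when the arms differ in spread or in the tail, which is plausible for lengths of stay. If the sample decides the branch, the reader of the final report cannot know from the plan which quantity was meant. Two trials drawn from the same population could report different ones.

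The wording also leaves room for judgement at two points, the normality assessment and the transformation, and staff know the allocation. What is at stake is how the secondary durations and the tertiary measurements are interpreted, not the trial's main conclusion.

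This is a rule that the document states. It is not a detail left to a later analysis plan.

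**Working it through.** **1. The plan's own figure, to set the scope.** The comparator rate comes from a cohort that "reported AKI in 30% of patients undergoing cardiac surgery", and the plan states that "the inclusion of 590 patients will achieve 80% power to detect a 10% absolute risk reduction in the risk of AKI" (two-sided 0.05, 1:1). With a pooled variance under the null:

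n per arm = [1.960·√(2·0.25·0.75) + 0.842·√(0.30·0.70 + 0.20·0.80)]² / 0.10² = (1.200 + 0.512)² / 0.01 ≈ 293.2, so 294 per arm and 588 in total.

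At 295 per arm the power is 80.2%. The 590 is reproduced. It rests on a binary outcome that this rule does not touch.

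**2. Which branch do the data choose?** The document gives no distributions, so these are assumed. The assumed rule is Shapiro-Wilk at 5% in each arm; if rejected and all values are positive, take logs and retest; Levene at 5% chooses Student or Welch; otherwise Mann-Whitney. There were 295 per arm, both arms identical, and 2,000 replicates.

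| Assumed population | Log-scale t/Welch | Raw-scale t/Welch | Mann-Whitney |
|---|---|---|---|
| Gamma, shape 20 | 52% | 5% | 43% |
| Gamma, shape 60 | 46% | 44% | 11% |

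A separate repeat of the shape-20 case gave 52%, 1% and 46%. The exact split moves, but the conclusion does not: one population is sent to different comparisons by chance. More strongly skewed data are routed more consistently. Gamma with shape 4 went to Mann-Whitney in about 98% of trials, and a lognormal with log-SD 0.6 went to the log scale in 91%.

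**3. Does this inflate type I error?** Over seven scenarios with identical arms, rejection ranged from 4.5% to 6.1%. The Monte Carlo standard error is √(0.05·0.95/2000) ≈ 0.5 points. There is no material inflation.

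**4. Do the branches differ in what they compare?** Take two lognormal arms with equal arithmetic means and log-SDs of 0.5 and 0.8. The gap in log means is (0.64 − 0.25)/2 = 0.195. Its standard error is √[(0.25 + 0.64)/295] = 0.055, so z = 3.55 and a log-scale test rejects in about 94% of trials. In simulation the rule rejected in 94.1%, and Welch on raw values in 5.7%. Both are correct answers to different questions, which is why the question has to be named first.

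**5. Does the Levene step help?** Allocation is 1:1 ("will be used to allocate participants in a 1:1 ratio"). With equal arms of size n, the pooled and the Welch standard errors are both √[(s₁² + s₂²)/n], so the t statistics coincide. Only the degrees of freedom differ: 588 for Student and at least 294 for Welch. The 5% critical values are 1.964 and at most 1.968. The step adds nothing.

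**6. Zeros and negative values.** The log is undefined for a negative fluid balance or a zero red-cell volume. In simulation, skewed fluid balance with negatives and red-cell volume with 55% zeros went to Mann-Whitney in 100% of runs, with rejection of 5.4% and 4.7% under identical arms. No run failed. The weakness is the summary: if more than half of each arm is untransfused, both medians are 0 whatever the difference in use.

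**7. Baseline albumin.** Adjustment multiplies the variance of the 24 h comparison by about 1 − r². For an assumed r of 0.3, 0.5 or 0.7 the reduction is 9%, 25% or 49%. Eligibility criteria {10} exclude albumin below 20 g/l, which implies that a baseline value exists.

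**The case against.** The best defence is that the procedure is conventional, keeps its error rate, concerns no primary analysis, and may be made specific in an analysis plan that is not shown. The first three points stand, and they limit the severity. The last helps only in part, because the article does not defer the choice; it states a data-driven one.

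Several stronger readings are tempting, and the material does not support them:

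- **A reader might infer that the rule breaks down for zeros or negative values.** It does not. The log applies only where suitable, and Mann-Whitney is the stated fallback.
- **A reader might take the gap between the rule and a comparison of means as harm from pre-testing.** With equal means and log-SD 0.6 v 0.7 or 0.6 v 0.8, the rule rejects in about 24% or 65% of trials, against about 4% for means. But always using Mann-Whitney rejects in 24% and 64%. With five-fold long stays in 5% v 10% of patients, the rule and fixed Mann-Whitney both detect the difference in 17%. These figures contrast ranks with means. They do not measure selection by the data, and they are not false positives, since the distributions really differ.
- **A reader might infer that a real difference in transfusion would be missed.** Only the median hides it. With assumed zero rates ten points apart, Mann-Whitney rejected in about 67% of runs and Welch in 59%.
- **A reader might speak of a formal normality pre-test.** Only Levene's test is named; the normality check is merely said to be an assessment. The simulations therefore test one assumed version of the rule.

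An unadjusted comparison of 24 h albumin is also valid. Adjustment is a gain in precision, not the correction of an error.

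**Conclusion.** The point holds as a minor one. For the three secondary durations and the five continuous tertiary outcomes, the plan lets an unspecified normality assessment and Levene's test on the trial data choose the scale, the test and the summary. Whether means, geometric means or ranks are compared is therefore not settled beforehand in an open-label trial.

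The size of the problem depends on the shape of the data. For mildly skewed outcomes the branch is close to a toss-up; for strongly skewed ones it is nearly predictable. These statements rest on assumed distributions and on Shapiro-Wilk at 5% as the normality check. The redundancy of the Levene step needs only near-equal arms.

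The remark on the red-cell median assumes that most patients are untransfused; the document gives no transfusion rate.

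**What to change.** Delete the normality-driven choice and the Levene step. Name one analysis, scale and effect estimate with 95% CI for each continuous outcome:

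1. **24 h albumin and net fluid balance:** mean difference from a linear model with unequal-variance standard errors, with baseline albumin as a covariate for 24 h albumin.
2. **ICU stay, hospital stay and ventilation time:** one pre-stated method, for example always rank-based, with an effect estimate and CI.
3. **Red-cell volume:** keep a valid test, and report the proportion transfused and the mean volume beside the median.
4. **Peak creatinine and haemoglobin at ICU discharge:** likewise one named method each.

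The cost is a few sentences in the protocol or analysis plan, with no new data and no further patients. The one real commitment is to a single estimand for the durations: a rank-based choice gives up sensitivity to a difference confined to a small group of very long stays, and a comparison of means does the reverse. That choice should be made on clinical interest before the data are seen.

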### Methods: participants, interventions and outcomes

#### Study setting {9}

Patients will be recruited at the following Australian hospitals: Monash Medical Centre, Cabrini Hospital, University Hospital Geelong, Prince of Wales Hospital, Prince of Wales Private Hospital and the Austin Hospital.

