### Methods for additional analyses {20b}

A subgroup analysis will be performed in patients with and without baseline renal insufficiency (eGFR < 60 mL/min/1.73 m^2^ or ≥ 60 mL/min/1.73 m^2^).

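### Randomisation is stratified by hospital and eGFR, but the stated primary test ignores both, which is valid but conservative if the strata predict AKI

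*Protocol article*

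**What the plan says.** - **Endpoint** (Protocol article, Outcomes {12}): "The primary outcome is the proportion of patients that develop AKI within hospital stay up to Day 28 post-enrolment". This is binary.
- **Randomisation** (Sequence generation {16a}): a permuted-block "randomisation sequence with fixed block size, stratified by hospital and eGFR", which "will be used to allocate participants in a 1:1 ratio". The abstract says the same in other words: centre and baseline renal function.
- **Sites** (Study setting {9}): six hospitals are named, "Monash Medical Centre, Cabrini Hospital, University Hospital Geelong, Prince of Wales Hospital, Prince of Wales Private Hospital and the Austin Hospital". With two eGFR levels, that makes up to 12 strata.
- **Analysis** (Statistical methods for primary and secondary outcomes {20a}): "Between-group comparisons will be performed using chi-squared tests for equal proportion". No stratified test, regression model or covariate is named in this section or elsewhere.
- **Other use of eGFR** (Methods for additional analyses {20b}): "A subgroup analysis will be performed in patients with and without baseline renal insufficiency". It is a subgroup factor only.
- **Non-adherence and missing data** ({20c}): intention-to-treat, a per-protocol sensitivity analysis and multiple imputation, but no adjustment for strata.

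The randomisation section splits eGFR into below 60 and above 60. The subgroup section splits it into below 60 and 60 or above. As written, a patient with an eGFR of exactly 60 has a subgroup but no randomisation stratum.

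**The concern.** Blocking within hospital and eGFR strata forces the arms to be nearly balanced on those factors. If the factors predict AKI, the estimated risk difference varies less from trial to trial than simple randomisation would allow. The ordinary chi-squared test does not know this: its variance still contains the between-stratum component that the design has removed. The standard error is then too large, the true type I error falls below 5%, and some power is left unused.

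The trial itself treats eGFR below 60 as important: it is an entry criterion for high risk, a stratification factor and the only named subgroup. To stratify on it and then leave it out of the primary test gives up part of what stratification buys. At stake is efficiency and correct coverage of the primary comparison, not protection against false positives.

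**Working it through.** **1. Reproduce the stated sample size.** Inputs from Sample size {14}: control risk 30% (a cohort that "reported AKI in 30% of patients undergoing cardiac surgery"), a 10-point absolute reduction to 20%, 80% power, two-sided 0.05; allocation 1:1. Pooled-variance formula without continuity correction:

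n per arm = [1.96·√(2·0.25·0.75) + 0.8416·√(0.30·0.70 + 0.20·0.80)]² / 0.10² = [1.96·√0.375 + 0.8416·√0.37]² / 0.01 = 293.2, rounded up to 294, so 588 in total against the stated 590.

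Power at 295 per arm = Φ{[0.10 − 1.96·√(0.375/295)] / √(0.37/295)} = 80.2%.

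The continuity-corrected formula would need 626. The stated 590 therefore matches the unadjusted, uncorrected test.

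**2. Closed-form check with two equal eGFR strata.** The control risks by stratum are assumptions; the document gives none. They average 30%, with exact 1:1 balance within strata. The unadjusted test uses the overall variance 0.30·0.70 = 0.21. The variance that actually applies is the mean within-stratum variance.

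- 30%/30% (not prognostic): the within-stratum variance is also 0.21, the ratio is 1, and type I error is 5%. There is no loss.
- 20%/40%: within-stratum variance (0.16 + 0.24)/2 = 0.20. SE ratio √(0.20/0.21) = 0.976. Type I error of the unadjusted test = 2·[1 − Φ(1.96/0.976)] = 4.5%.
- 15%/45%: within-stratum variance (0.1275 + 0.2475)/2 = 0.1875. SE ratio √(0.1875/0.21) = 0.945. Type I error = 2·[1 − Φ(1.96/0.945)] = 3.8%.

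For power with a 10-point reduction in each stratum, let V₀ be the variance sum that the test uses and V₁ the variance sum that applies. Power = Φ{[0.10 − 1.96·√(V₀/295)] / √(V₁/295)}.

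- 20%/40% against 10%/30%: V₁ = 0.20 + 0.15 = 0.35. Unadjusted V₀ = 0.375 gives 80.9%; stratified V₀ = 0.355 gives 82.4%.
- 15%/45% against 5%/35%: V₁ = 0.1875 + 0.1375 = 0.325. Unadjusted V₀ = 0.375 gives 81.8%; stratified V₀ = 0.33 gives 85.0%.

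Simulation of the same two cases agrees: 81.1% against 82.5%, and 82.1% against 85.4%; unadjusted type I error 4.6% and 3.8%.

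**3. Simulation with both factors.** 40,000 trials per scenario, 6 hospitals × 2 eGFR strata, exact balance within strata, overall risks held at 30% against 20% for power and 30% in both arms for type I error. Rounding strata to whole patients gave 594 to 596 patients, so the baseline power is slightly above 80.2%. CMH is the Cochran-Mantel-Haenszel test on all strata. OR is the eGFR odds ratio; SD is the spread of hospital effects on the logit scale. Ranges cover an eGFR-below-60 share of 50% or 70%.

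| Assumed strength | Power, chi-squared | Power, CMH | SE ratio | Type I error, chi-squared |
|---|---|---|---|---|
| OR 1, SD 0 | 80.8% | 80.7% | 1.00 | 5.0–5.1% |
| OR 2, SD 0.3 | 81.2–81.5% | 82.2–82.3% | 0.98 | 4.4–4.5% |
| OR 3, SD 0.3 | 81.4–81.6% | 82.7–83.3% | 0.97 | 4.3% |
| OR 4, SD 0.6 | 81.8–82.8% | 85.2–86.4% | 0.93–0.94 | 3.4–3.5% |

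The CMH test stayed near 5% throughout (4.8% to 5.3%). At the strongest setting the SE ratio of 0.93 to 0.94 means that the unadjusted standard error is roughly 7% too large.

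**The case against.** The best defence is that nothing in the plan breaks. The test is valid, its error is on the conservative side, and 590 patients deliver the promised power with it. That stands, and it limits the point to unused efficiency.

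Second, the document does not show that the strata are prognostic. The operative risk factors listed in its background include procedural complexity but not baseline eGFR. Under the eligibility criteria, patients with eGFR of 60 or more can enter only through a combined, multi-valve or thoracic aortic procedure. The eGFR contrast inside the trial could therefore be weak. This also stands, and is why the result is a range that starts at zero.

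Third, a separate analysis plan might add adjustment. It might, but the article does more than stay silent: it names the test.

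A reader might infer more than the document supports:

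- *That the trial is underpowered because of this test.* It is not: power is 80.2% at 590. An assumed 25%/55% split gives an unadjusted power of only about 74%, but its control risk averages 40%, and the plain formula for 40% against 30% at 295 per arm already gives 72%. That shortfall comes mainly from the event rate.
- *That power falls to 77.5%.* This holds only for a continuity-corrected test, which the article does not specify.
- *That the missing effect measure, interval or interaction test is an error, or that peak creatinine is fixed as an unadjusted comparison.* An article commonly leaves the first three to the full protocol or analysis plan. Peak creatinine is a tertiary outcome, and the methods section is headed for primary and secondary outcomes.

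**Conclusion.** The point holds as a mismatch between a stated design and a stated analysis. Randomisation is stratified by hospital and eGFR; the primary test uses neither. If those factors predict AKI to a moderate or strong degree, the chi-squared test runs at about 3.4% to 4.6% type I error and forgoes about 1 to 4 points of power, with 1 to 2 points in the middle scenarios. With weak strata the loss is negligible, and with non-prognostic strata it is zero.

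The direction is certain. The size rests on assumed stratum risks, odds ratios and hospital spread, and on near-exact balance within strata. It does not make the trial's significance claim unsafe or undermine the sample size. It is a worthwhile improvement at little cost. The differing eGFR boundary is a small separate inconsistency in the same stratification factor.

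**What to change.** - Make the primary analysis a Cochran-Mantel-Haenszel test with a Mantel-Haenszel risk difference and 95% CI over hospital and eGFR stratum. Alternatively, fit a logistic regression on treatment, hospital and eGFR stratum and report a standardised risk difference with 95% CI.
- Prespecify how sparse hospital strata are merged. With up to 12 strata the average is 590/12 ≈ 49 patients, and small hospitals may have far fewer.
- Keep the chi-squared test, stated to be without continuity correction so that it matches the sample size calculation, as a sensitivity analysis.
- Word the upper eGFR stratum in the randomisation section as in the subgroup section (60 or above), after checking how the randomisation system classifies a value of exactly 60.

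Cost: wording only. Hospital and eGFR stratum are needed for randomisation anyway, and no extra patients are required. There is a small downside: the merging rule must be written, and the plan must say how the stratified estimate is combined across multiply imputed data sets. The change should be fixed before outcome data are analysed by arm, so that the choice between adjusted and unadjusted results is not open afterwards.
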